#### Intervention and randomisation.

Baobab fruit powder will be supplied by the African Baobab Alliance (ABA), a not-for profit sector organisation representing multiple stakeholders in the Baobab sector, including Baobab fruit harvesters from underserved rural Southern African communities. The BFP provided for this study is a certified organic and natural product and is available in South African supermarkets. It is derived from fruit of the baobab tree that are free-harvested by rural harvesters in the Limpopo Province, South Africa. The BFP surrounds the seeds that are protected by a hard shell. The processing of the fruits includes opening the fruit, separating the seeds from the powder and then milling, sieving and packaging the powder for consumption.

For the trial, the BFP group will consume 16 g BFP daily for 45 days, while the control group will consume 13.5 g placebo containing tapioca flour and citric acid with a similar appearance and taste to the BFP. The 16 g dose of BFP was selected based on serving suggestions of commercially available products which vary between 8 and 24 g per day. The selected 16 g dose is equivalent to 2 heaped tablespoons and will deliver approximately ~8 g of dietary fibre per day. Previous studies reported long-term use (tolerability) [39], palatability [30], significant changes in postprandial glycaemia [27,28] and insulin response [29] with dosages of 16 g and above. The duration (45 days) was based on studies reporting statistically significant differences in the Lac/Man ratio between the respective intervention and placebo-treated groups [15,40]. To our knowledge, there were no similar studies using a placebo-controlled design to guide the choice of the placebo treatment. The texture and appearance of tapioca flour is similar to BFP, which is important when considering that some participants may be familiar with BFP. Furthermore, tapioca flour does not contain significant levels of dietary fibre (~0.6 g per 100 g), consists predominantly of carbohydrates and contains minimal amounts of other nutrients (https://www.natureschoice.co.za/shop/tapioca-flour-2/). As our study hypothesis is based on the fibre content of BFP (~50%), tapioca flour can be regarded as inert in this context. Therefore, the placebo was chosen to contain tapioca flour (12 g) to mimic the appearance and citric acid (1.5 g) was chosen to mimic the taste of BFP. Citric acid is an organic acid commonly found in fruits and specifically also in Baobab fruit powder [1,6]. The dose for the placebo (13.5 g per day containing ~0.07 g fibre) was calculated to deliver the same energy content as the 16 g BFP (~160 kJ), which is equivalent to half a slice of bread and thus contributes a minor addition to the daily energy intake of our participants. The carbohydrates in tapioca flour are unlikely to have a significant glycaemic impact, however, fasting glycaemia and insulin resistance will be assessed in all participants before and after the intervention. The sachet contents of BFP and placebo can be suspended in up to 1 L of water or added to other cold beverages such as smoothies and juices, or even to cereals. The participants will be encouraged to maintain their usual dietary and lifestyle behaviours during the intervention period. While our study hypothesis is based on the fibre content, BFP, as a food, is also a source of minerals and vitamins [1,6], which may potentially affect gut and cardiometabolic health markers. These vitamins and minerals are integral to the fruit pulp and its properties and should not be considered as confounders. The daily dose of 16 g BFP to be consumed during the intervention would deliver ~20 mg vitamin C, ~ 290 mg Potassium, ~ 30 mg Magnesium and ~50 mg Calcium, based on typical nutritional analysis data [6].

The intervention and placebo powder were packaged in foil sachets protected from light by Joypak, Cape Town, South Africa, with non-identifiable labels to ensure that both study staff and participants will be blinded to the group randomisation/allocation. Participants will be block randomised at a 1:1 ratio with random permuted block sizes of 2 and 4 while applying *a priori* stratification for sex. Researchers will use the randomisation module on RedCap to allocate a randomisation number to the participants on the day of baseline testing. Participants, investigators, analysts and statistician will be blinded to the group allocation. In the event that unblinding becomes necessary, two independent SAMRC staff members who are not directly involved in the study will be able to identify specific codes.

#### Pre- and post-intervention testing.

On the baseline and follow-up testing days, participants will attend the research facility following a 10–12 hour overnight fast. For 48 hours prior to these testing sessions, participants will be requested to avoid strenuous exercise, alcohol, non-nutritive sweeteners (e.g., in chewing gum and beverages), spicy food, caffeine (including tea), sporadic over-the-counter medication (such as headache pills or other nonsteroidal anti-inflammatory drugs) and supplement use [37,38].

**Stool sampling:** Participants will be given an EasySampler kit to take home for the collection of a pre- and post-intervention stool sample for microbiota analysis. The fresh sample will be aliquoted at the research facility within 6 hours. A pea-sized aliquot of the fresh sample will be removed using a sterile swab and stored in a cryovial prior to microbiota analysis. Approximately 1 g of stool will be weighed for SCFA analysis and all samples will be stored at −80°C.

**Blood sampling:** A fasting venous blood sample (~45 ml) will be collected for the subsequent determination of plasma glucose, serum insulin, serum lipids (triglycerides, total cholesterol, HDL cholesterol and LDL cholesterol), inflammatory markers (e.g., high-sensitivity C-reactive protein [hs-CRP] and biomarkers of intestinal permeability (e.g., LPS, LPS-binding protein [LBP], soluble cluster of differentiation 14 [sCD14], intestinal fatty acid binding protein [IFABP]) as well as safety endpoints (creatinine, aspartate aminotransferase [AST], alanine aminotransferase [ALT], alkaline phosphatase [ALP], gamma glutamyltransferase [GGT]).

**Lactulose/Mannitol test:** The intestinal permeability lactulose/mannitol (Lac/Man) test will be conducted as described by Seethaler *et al.* [37] and Khoshbin *et al.* [38]. A urine sample (30 ml) will be collected prior to the test to account for baseline levels of mannitol and lactulose. Lactulose (5 g, Dulphalac, Clicks, South Africa) and mannitol (2 g, Merck Life Science, Darmstadt, Germany) will be dissolved in 200 ml water to be consumed within 5 minutes by the participants to initiate the test procedure. Cumulative urine will be collected for 24 hours, of which the first 5 hours will be collected at the research facility (estimated small intestinal permeability). Participants will be provided with water and a meal after 2 hours. The participants will collect their urine for a further 19 hours in provided containers (estimated large intestinal permeability). The 5-hour and 24-hour urine volumes will be recorded, and aliquots will be stored at −80 °C before liquid chromatography/mass spectrometry (LC/MS/MS) for the quantification of lactulose and mannitol.

**Blood pressure and anthropometry:** Determination of blood pressure, weight and height measurements are described in the screening section. Waist circumference will be measured in the mid–axillary line at the midpoint between the lower margin of the last palpable rib and the top of the iliac crest at the end of normal exhalation, and hip circumference at the largest protrusion of the buttocks. Both will be measured to the nearest 0.1 cm. Whole body composition will be estimated using a Quantum Legacy Bioelectrical Impedance Analyser (BIA, RJL Systems, USA). Blood pressure, weight, hip and waist circumference and whole-body composition will be taken every 2 weeks at the participant visits to the research facility.

**Lifestyle and sociodemographic characteristics:** Lifestyle, health and socio-demographic information will be collected using validated questionnaires [31,32]. This includes age, sex, self-reported ethnicity and family history of disease. Gastrointestinal symptoms [41,42] and stool consistency will be assessed (Bristol stool chart) [43]. Perceived stress [44] and lifestyle factors, including previous smoking habits and alcohol intake will also be determined. Socio-economic status will be assessed based on factors such as education level, occupation, employment status and housing. In addition, physical activity will be estimated using the validated Global Physical Activity Questionnaire (GPAQ) [45]. Dietary intake will be estimated using a 3-day food record, including 2 non-consecutive weekdays and one weekend day. Nutrient intake will be analysed using the South African Food Composition Database System (SAFOOD, the South African Food Composition Database, South African Medical Research Council, Cape Town, South Africa) [32].

#### Safety and progress monitoring.

Participant compliance, tolerability, acceptability and symptoms will be monitored weekly through alternating telephonic contact and visits at the research facility. Participants will be asked about any side effects, any adverse events, including gastrointestinal symptoms, and stool consistency. Should any adverse events occur, the participant needs to contact study staff and will be referred to the study physician and to a healthcare facility, if necessary. During the biweekly in-person visits, participants will be requested to return used and unused sachets for accountability and receive the next batch of investigational product. In the event that a participant develops an unrelated illness (such as a cold of flu) and requires medication, the study physician will assess whether the participant needs to be excluded.

At the first in-person follow up session (after 2 weeks), a blood sample for safety endpoints, including kidney (creatinine) and liver function (AST, ALT, ALP, GGT), will be collected.

A steering committee consist of four independent and experienced scientists and two investigators who are part of the trial team. This committee will provide oversight over the conduct of the trial and to safeguard the interests of study participants. The steering committee will be responsible for (i) assessing the safety aspects of study procedures (e.g., review of the research protocol, informed consent documents and plans for data safety and monitoring), (ii) for monitoring the overall conduct of the study (periodic assessment of participant recruitment and retention) and (iii) report on safety and progress of the trial. Should any participants present with abnormal clinical values before or during the study, they will be referred to the study clinician and assessed for further referral and/or treatment.

The stopping rules for this study include the following:

Should there be 10 or more serious adverse events (SAEs) that are judged by the study clinician to be related to the investigational product, the study will be stopped. Participation in the trial will be stopped for individual participants should there be any renal dysfunction detected, any study-related allergic reaction, liver function test results more than 2-fold above the upper normal limit or when participants present with gastrointestinal symptoms with no other obvious cause that warrant discontinuation of the investigational product and further participation in the study. These gastrointestinal symptoms include abdominal pain, nausea or diarrhoea more than 3 times per week in 2 consecutive weeks and significantly more frequent than at baseline.

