## Methodology

### Study design

In this randomised double-blind, placebo-controlled trial, 50 apparently healthy women and men living with obesity will be randomised at a 1:1 ratio into an experimental (BFP) or a control (placebo) group. Both BFP and the isocaloric placebo will be consumed daily for 45 days.

The schedule of enrolment, intervention and assessments is outlined in Fig 1. Prior to and following the 45-day intervention, participants will complete one testing session, during which the primary and secondary outcomes as well as potential confounders will be measured. To assess safety of BFP, liver (liver enzymes) and kidney (estimated glomerular filtration rate, GFR) function will be assessed at baseline, 2-weeks into the intervention and following the 45-day intervention. Gastrointestinal symptoms will be assessed weekly using validated questionnaires. Participants will be monitored weekly by alternating telephonic contact and visits to the research facility to confirm compliance, acceptability and tolerability. Adverse events, such as allergic reactions, and incidence of other potentially confounding health issues such as illnesses that require extended use of medication will also be assessed. The participants will be encouraged to maintain their usual dietary and lifestyle behaviours during the intervention period. Participants will be reimbursed for their time and travel costs. The overview of the study design is described in Fig 2.

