### Statistical analysis

#### Sample size determination.

The study is powered on the primary study endpoint, the Lac/Man ratio, which is based on the data reported by del Piano *et al.* [40] for a similar treatment period. Considering a mean ± standard deviation (SD) difference in the Lac/Man ratio between treatment and control groups (0.015 ± 0.006 versus 0.021 ± 0.007) after the 45-day treatment [40], significance level of p < 0.05 (two-sided test) and power of 80%, 20 participants per group would be sufficient for our study to detect significant differences. When factoring in a drop-out rate of 25% (5/25), 25 participants were selected per group. In the unlikely event that there is a dropout of greater than 25%, we will recruit additional participants until we meet the required sample size.

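### The only trial-level stopping trigger stated, 10 related serious adverse events, is too high for 50 apparently healthy volunteers

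*Protocol article*

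**What the plan says.** The stopping rules are in the protocol article under Safety and progress monitoring. The lead-in is "The stopping rules for this study include the following", and one trial-level rule follows: "Should there be 10 or more serious adverse events (SAEs) that are judged by the study clinician to be related to the investigational product", in which case the study stops. It counts events rather than people, and it is not restricted to the BFP arm. No reason is given for the number ten.

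The remaining criteria act on single participants: "Participation in the trial will be stopped for individual participants should there be any renal dysfunction detected, any study-related allergic reaction", liver tests above twice the upper normal limit, or defined persistent gastrointestinal symptoms. The same section provides weekly contact, liver and kidney bloods at two weeks, and a steering committee of four independent scientists and two investigators. The committee's tasks include to "report on safety and progress of the trial". No event count is attached to them.

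Study design gives the population: "50 apparently healthy women and men living with obesity will be randomised at a 1:1 ratio". Sample size determination gives the arm size: "25 participants were selected per group". On blinding, Intervention and randomisation says "Participants, investigators, analysts and statistician will be blinded to the group allocation". If unblinding is needed, "two independent SAMRC staff members who are not directly involved in the study will be able to identify specific codes".

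**The concern.** A trial-level stopping rule should act while there are still people to protect, and at a risk that nobody would accept for the population concerned. These volunteers are screened to be free of chronic disease and take a food that is sold in supermarkets. An SAE judged related to such a product should be rare, and a handful would already call the trial into question. A trigger of ten lets that handful, and several more, accumulate before the stated rule requires anything at trial level.

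Confirming that BFP is safe to consume is a stated secondary aim in the Introduction, so the threshold also bears on something the trial sets out to show. What is at stake is participant protection and the credibility of the safety conclusion. The efficacy analysis is not affected.

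**Working it through.** **Inputs from the protocol article.** Trigger: 10 related SAEs (Safety and progress monitoring). Randomised: 50 (Study design), 25 per arm (Sample size determination). The article gives no expected SAE rate, no tolerable risk and no operating characteristic for the rule, so there is no stated figure to reproduce. All risks below are assumptions, shown as a range.

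**Step 1: the trigger as a proportion, at one SAE per person.**
- Both arms: 10/50 = 20%.
- All events on BFP: 10/25 = 40%.

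**Step 2: chance that ten events are reached by the end of the trial, at one SAE per affected person.** For n people at common risk p, the exact binomial tail is P(X ≥ 10) = Σ from x = 10 to n of C(n,x) p^x (1−p)^(n−x). Where placebo has its own risk q, X is the sum of independent Bin(25, p) and Bin(25, q). A placebo event can count because the clinician's judgement is made under blinding.

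| Who carries the risk | p = 10% | p = 20% |
|---|---|---|
| BFP only (n = 25) | 0.00008 (about 0.01%) | 0.0173 (1.7%) |
| BFP at p, placebo at 1% | 0.00023 (0.02%) | 0.0257 (2.6%) |
| BFP at p, placebo at 5% | 0.0034 (0.34%) | 0.0822 (8.2%) |
| All 50 at p | 0.0245 (2.5%) | 0.556 (56%) |

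With risk on BFP only, the probability at p = 30% is 19%, and an even chance of triggering needs a true risk of about 38%.

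**Step 3: repeat events.** Because events are counted, repeats make the rule more sensitive. If each affected person has two related SAEs, five people produce ten events, so the tail becomes P(X ≥ 5). At p = 10% this is 0.098 (9.8%) for BFP only and 0.569 (57%) for all 50.

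**Step 4: a pooled pause when 3 participants have had a related SAE, P(X ≥ 3).**

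| Who carries the risk | 1% | 5% | 10% |
|---|---|---|---|
| BFP only (n = 25) | 0.0020 (0.2%) | 0.127 (13%) | 0.463 (46%) |
| All 50 | 0.0138 (1.4%) | 0.459 (46%) | 0.888 (89%) |

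With 5% on BFP and 1% on placebo the probability is 0.188 (19%).

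These probabilities describe the stated counts alone. They are not the chance that the trial would run on unexamined, because the committee can act without a count.

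**The case against.** The strongest reply is that ten events is a mandatory stop and was never meant to be the first alarm. Nothing says that the committee must sit idle at one to nine events; it has a general duty to protect participants and a majority of independent members. The wording of the lead-in leaves room for further rules in the full protocol, and the committee also reviews data safety and monitoring plans that are not shown. Two ethics committees and the national regulator have approved the trial. The individual rules act from the first affected person and cover the foreseeable harms. Related-SAE risks of 10% to 20% are remote for an authorised food with earlier human use. At a 1% risk the proposed pause would itself almost never fire, and at 5% in both arms, with no excess on BFP, it would pause the trial 46% of the time. Finally, recruitment was expected to end by September 2025 and follow-up by October 2025, so little may be left to protect.

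Much of this stands. The safeguards are real, other rules may exist elsewhere, the benefit is limited, and what counts as too high is a judgement. None of it supplies a lower trial-level count or a reason for ten. The individual rules protect the person already affected; they do not say when enrolment and dosing of others should be reconsidered. That high risks are unlikely does not justify the threshold either: a stopping rule exists for the unlikely case, and this one would seldom act there unless both arms share a risk near 20% or events recur within people.

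**Conclusion.** The concern holds, as a recommendation with medium confidence. The stated trigger corresponds to 20% of all participants or 40% of the BFP arm at one SAE each. At an assumed 10% related-SAE risk with one SAE each, it would be reached with probability between about 0.01% and 2.5%, depending on how far placebo participants share the risk. It becomes reasonably sensitive only if all 50 carry a risk of about 20%, or if affected people have repeat events.

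This rests on assumed risks, on independence between participants, and on the view that a 10% risk of a related SAE is unacceptable in healthy volunteers taking a food. It concerns the number ten as stated, not the absence of detail that the full protocol may contain.

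**What to change.** Amend the stopping rules under Safety and progress monitoring so that the trial pauses for steering committee review once a low number of participants, for example 3, have each had at least one SAE judged related. Count people rather than events for this pause, and pool the arms so that no unblinding is needed to apply it. If the committee then needs the allocation, the two independent code holders can supply it. Keep ten events as the mandatory stop. The committee should choose the final number and record the reason, since 3 is only an illustration.

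The cost is a short amendment with ethics and regulator notification, and the possibility of pausing at a risk that proves tolerable. If all 50 carry the same risk, a pause at 3 has a 1.4% chance at a 1% risk and 46% at 5%. A pause prompts review and does not end the trial. The primary analysis and its power do not change. If follow-up has already finished, the amendment can protect nobody.

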#### Statistical analysis.

Results will be presented as means ± SD or medians and interquartile ranges for normally and skewed data, respectively. Non-normally distributed data will be transformed for parametric analysis. Intention to treat analysis approach will be used. A mixed effects model will be used to compare within and between groups (control and BFP) differences in primary and secondary outcome variables adjusting for potential confounders as outlined in Table 1. Data will be analysed using STATA SE (version 17, StatCorp, Texas, USA).

Statistical comparisons for taxonomic differences will be performed using Songbird [54], an experimentally validated, compositionally coherent differential abundance method. Statistical visualization of reference frames from Songbird will be performed using Qurro [55], which forms part of a compendium of PCA/PCoA visualization tools such as EMPress [56] and EMPeror [57], designed for the analysis of microbiome datasets. For longitudinal data we will employ volatility analyses, such as semivariograms [58] and Compositional Tensor Factorization [59], to decompose time-series responses into components acting on different timescales. Using these approaches, we will identify taxa that are associated with Baobab fruit powder supplementation, faecal SCFA production, biomarkers of intestinal permeability (LPS, LBP, sCD14, IFABP) and cardiometabolic parameters including glucose, insulin, lipid profiles, inflammatory markers across intervention groups.

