## Discussion

Although BFP has been consumed by humans for centuries [60], to the best of our knowledge, this is the first study to explore the potential effects of regular consumption of BFP on intestinal barrier function and gut microbiota diversity in humans. Further, this study will likely advance our understanding of the relationship between intestinal permeability and cardiometabolic risk in humans. There is limited scientific evidence on the sustained effects of BFP in humans. To date our understanding is based on observational studies or acute studies in healthy participants who received once-off treatments [27,29,30]. The outcomes of the study may stimulate further research exploring the effects and mechanisms of action of BFP, including studies in populations with metabolic and other diseases.

A challenge will be the potential for participants to fall ill and require prescription medication such as antibiotics and anti-inflammatory medication. We used a 25% dropout rate to calculate the required sample size to accommodate for incidence of such illnesses. A further limitation presents the reliance of self-reported data such as health status, dietary intake and adherence to the dietary and lifestyle recommendations prior to the Lac/Man test, which may affect the study outcomes.

As the study population comprises relatively young individuals (aged between 25 and 55 years) without known diseases, this may not be representative of the general population. The selection criteria were chosen to minimise confounding factors due to the small sample size. A further limitation is that participants may be unaware that they have chronic diseases, for example HIV, which can affect intestinal permeability [61]. This study will rely on self-reported HIV status to exclude participants living with HIV, which may be prone to errors. Future studies can explore the effectiveness of BFP in a broader population including participants living with HIV, as well as in participants with metabolic diseases such as type 2 diabetes and hypertension.

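### The stopping rules end trial participation rather than product intake alone, so the day-45 Lac/Man value is lost and the intention-to-treat analysis is undercut

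*Protocol article*

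**What the plan says.** The individual stopping rules are under Safety and progress monitoring in the protocol article: "Participation in the trial will be stopped for individual participants should there be any renal dysfunction detected". The sentence goes on to study-related allergic reaction, liver tests more than 2-fold above the upper normal limit, and gastrointestinal symptoms that warrant "discontinuation of the investigational product and further participation in the study". That last clause names product and participation separately and ends both.

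The same section has a second route out. If a participant falls ill for an unrelated reason and needs medication, "the study physician will assess whether the participant needs to be excluded".

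On timing, Study design says: "Prior to and following the 45-day intervention, participants will complete one testing session". The Lac/Man test belongs to that session. The two-weekly visits add safety bloods (at week 2), blood pressure and anthropometry, but no Lac/Man test.

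On analysis, the Statistical analysis section says "Intention to treat analysis approach will be used" and "A mixed effects model will be used to compare within and between groups (control and BFP) differences in primary and secondary outcome variables".

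On dropout, Sample size determination allows for 5 of 25 per group and recruits further participants if dropout exceeds 25%. The Discussion, speaking of participants who fall ill and need prescription medication, adds: "We used a 25% dropout rate to calculate the required sample size to accommodate for incidence of such illnesses".

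**The concern.** An intention-to-treat comparison needs outcomes from everyone randomised, whether or not they still take the product. These rules tie the two together: whoever meets a criterion leaves the trial as well as the product. With only one Lac/Man measurement after baseline, nothing later stands in for it.

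For such a participant the mixed model has a baseline value only. The day-45 contrast then rests on those who stayed, plus the assumption that, given the observed data, those who left would have had similar values. This is hard to defend for stops that the product itself may cause. BFP supplies about 8 g of fibre a day and the placebo about 0.07 g, so unequal stopping for gastrointestinal symptoms is plausible. The protocol's own Table 1 treats gastrointestinal disease as affecting permeability. If stopping is related to permeability and differs between arms, the comparison at day 45 is no longer the randomised one. Recruiting replacements restores the numbers but not the comparison.

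**Working it through.** **1. The plan's own figure.** Inputs from Sample size determination: "0.015 ± 0.006 versus 0.021 ± 0.007", two-sided 5%, power 80%.

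- Pooled SD = √((0.006² + 0.007²)/2) = √0.0000425 = 0.00652.
- Standardised difference = 0.006/0.00652 = 0.92.
- Normal approximation: n = 2(1.96 + 0.84)²/0.92², which rounds up to 19 per group.
- Noncentral t: power 0.788 at 19 and 0.810 at 20, so 20 per group. The plan's figure reproduces.
- Allowance: 20/(1 − 5/25) = 25 per group.

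The sample size thus plans for up to 5 people per arm without a day-45 value. Power is 0.810 with 20+20 measured, 0.851 with 20+25 and 0.890 with 25+25. The last figure is an upper limit on what complete follow-up gains, because values taken off product would dilute the effect.

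**2. The sections side by side.**

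| Section | What it does to a stopped participant |
|---|---|
| Safety and progress monitoring, stopping rules | Ends trial participation; for gastrointestinal symptoms, product and participation together |
| Safety and progress monitoring, illness | Possible exclusion after randomisation, case by case |
| Study design | Lac/Man at baseline and after day 45 only |
| Sample size determination | Recruits more if dropout exceeds 25% |
| Statistical analysis | Intention to treat, mixed model |

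Nothing in the article brings a stopped participant back for day 45. The loss of the outcome is therefore an inference from ended participation, not a stated rule.

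**3. How much it could matter.** The document gives no stopping rates, so this is an illustration on assumed ones. There is no true effect and 25 per arm. The day-45 outcome Y is standard normal, rescaled by 0.00652. Loss follows logit P(loss) = a + kY, with a set in each arm to give the stated loss rate. Observed day-45 means are compared over 20,000 simulated trials per setting. With k = 1 per SD:

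| Loss, BFP/placebo | Spurious difference | Share of 0.006 | Type I error |
|---|---|---|---|
| 20%/20% | 0 | 0% | about 5% |
| 8%/4% | about −0.0002 | 4% | about 5.3% |
| 12%/4% | about −0.0005 | 8% | 5.4% to 5.7% |
| 28%/12% | about −0.0008 | 14% | about 7% |
| 32%/8% | about −0.0013 | 21% | 9.4% to 9.6% |

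Where a range is given, repeat runs differed by simulation error; near 5% the standard error is √(0.05 × 0.95/20,000) = 0.0015. The 8%/4% row is therefore barely distinguishable from nominal.

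Varying the slope k from 0.5 to 1.5 gives 8% to 18% of the planned effect for the 28%/12% split and 12% to 27% for 32%/8%.

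The two larger splits average (28 + 12)/2 = (32 + 8)/2 = 20%. They treat the whole dropout allowance as outcome-dependent. The negative sign comes from assuming that high Lac/Man values are lost more often and that more are lost on BFP. If either assumption is reversed, so is the sign.

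**The case against.** Missing outcomes do not in themselves contradict intention to treat, and no sentence cancels the day-45 visit or drops anyone from the analysis set. Exclusion by the physician is not said to mean exclusion from the analysis. A reader might infer that the plan has become a completers analysis and that its intention-to-treat claim is void. The document does not go that far. What stands is narrower: conduct rules that, followed literally, leave the stated analysis without its data.

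A reader might also take the Discussion as confirming that everyone stopped is counted as a dropout. It speaks only of illness needing prescription medication and is silent on the renal, liver, allergy and gastrointestinal stops. Illness exclusions concern unrelated conditions and are judged case by case by blinded staff, so a link to treatment arm is conjecture there.

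The illustration is also open to challenge. Ordinary withdrawals, which rewording would not recover, are counted as if the rules caused them. The gastrointestinal criterion is demanding (more than 3 times a week in 2 consecutive weeks, and well above baseline), and the article cites earlier tolerability at 16 g and above. The simulation ignores baseline Lac/Man, which the mixed model could use to absorb loss that depends on baseline permeability. These points lower the likely size and rule out any claim about direction.

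Handling of missing data can properly be left to the analysis plan. The scope of the stopping rule cannot, because no analysis plan recovers urine that was never collected.

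**Conclusion.** The point holds as a should-fix. The stopping rules are stated and are scoped to the trial rather than to the product. With Lac/Man measured only twice, following them literally removes the primary outcome and leaves the intention-to-treat analysis dependent on a missing-at-random assumption. That assumption is weakest for stops that the product may cause, such as gastrointestinal symptoms.

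It would be tempting to conclude that the result will be biased in favour of BFP. The document does not support this: bias needs outcome-related loss that differs between arms, and neither its direction nor its size can be known from the text. On the assumptions shown, it ranges from negligible at small imbalances to about a fifth of the planned effect, with type I error near 10%, at a large one. Equal losses give none.

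**What to change.** Reconcile Safety and progress monitoring, Sample size determination and Statistical analysis by separating the end of product intake from the end of follow-up. The clinical criteria and the physician's safety decisions stay unchanged. State that:

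- all randomised participants, whatever their product use or medication, are invited to the already planned day-45 testing where the physician considers it safe and they still consent;
- all are analysed in the group to which they were randomised;
- exclusions for illness or medication apply only to a sensitivity (per-protocol) analysis;
- any additional recruits are added to those already randomised and do not replace them in the analysis.

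If day-45 testing of stopped participants is already intended, one sentence saying so is enough.

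The visits are already planned for 50 participants, so the extra testing costs little. The change does need an amendment under two ethics committees and a regulator, during follow-up that was due to finish in October 2025, and it cannot recover anyone already stopped. Some values will be taken off product and will dilute the effect. Lac/Man may be hard to interpret in participants stopped for renal reasons, because it is a urinary test; flag those values in a sensitivity analysis. If follow-up has already closed, report the stops by arm and reason, and examine how the primary result depends on the missing-at-random assumption.
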